### ii. Secondary outcomes

- The relationship between whether or not ECI is achieved during cooling before DHCA and clinical outcome measures.
- The duration of ECI (minutes) and its relationship with clinical outcome measures.
- The morphology, amplitude and continuity of EEG activity during hypothermia, DHCA, selective antegrade cerebral perfusion (SACP) and rewarming to normothermia.
- Pre- and postoperative background EEG patterns and seizure burden (absent, present, status epilepticus). This will be assessed retrospectively by specialist clinical neurophysiologists, with reference to published articles.

## 6. Follow-up

All patients will be followed for 30 days or until hospital discharge, whichever is sooner. A follow-up sub-study will be conducted at approximately 2 years following surgery, to identify whether perioperative EEG activity is associated with long-term neurodevelopmental outcome. With consent, the parents or guardians of participants will be re-approached at 22-26 months following surgery to participate in the SAFE-Follow-up of Infant Neurodevelopment (SAFE-FIN) sub-study. With additional consent, neurodevelopmental outcome will be assessed by a trained physiotherapist using the Bayley-III scale of infant development. Additional information on this sub-study is provided in the Appendix.

## 7. Sample size calculation

During the feasibility phase, 17/30 (56%) patients achieved ECI before DHCA at a mean temperature of 22.6°C (SD  $\pm$ 2.9). We estimate that by recruiting a total of 74 participants, 41 will achieve ECI before DHCA with the same mean temperature at ECI with a 95% confidence interval around the estimate of  $\pm$ 0.9°C. There is no robust data on the rate of the secondary outcomes in neonatal aortic arch repair so these will be considered exploratory.

## 8. Statistical analysis

Baseline and procedural characteristics will be summarized using median with interquartile ranges, or mean with standard deviation for continuous variables, and counts with percentages for categorical variables. Study feasibility will be measured by counts and percentages of successful patient recruitment,

data collection procedures and technically successful EEG recordings. The temperature (degrees Celsius) and variability ( $\pm$ SD) at which ECI is achieved and evolution of continuity will inform EEG utility in cardiac surgery. Secondary analysis will compare demographic, clinical and EEG variables between those with ECI at DHCA and those without to identify subgroups which may require increased neurocritical care resource.

## **9. Ethical considerations**

Ethical approval will be sought via the integrated research application system (IRAS), NHS Research Ethics Committee (REC), health research authority (HRA) and the research and development office at BCH. The analysis of the EEG may have clinical significance. Seizures, epileptiform activity, immaturity, and evidence of HIE will be disclosed to the participant's clinical team.

## **10. Data handling**

### **i. Data collection**

The CRF and cardiac database are the primary data collection instruments for the study. All data requested must be recorded and missing data must be explained. The CRF or emailed data sheets can be printed off in paper form but must be kept in the master site file. Access to Intellivue X data will be made available to the PI via the PICU study collaborators.

### **ii. Data monitoring**

Data from CRFs and the cardiac database will be inputted into an electronic database and stored within a secure network at BCH which will be maintained by the PI. Data entered will be checked for missing or unusual values via range checks. If any problems are identified the PI will inform the CI and resolve the issue.

The original signed consent form will be stored in the master site file and copies given to the parent or guardian and placed in the medical notes. Individual participant medical information obtained as a result of this study is considered confidential. CRFs and EEG data will be identified by unique study identifiers only.

### **iii. Data sharing**

In the event of collaborations with centres, both within and outside of the United Kingdom, pseudonymised EEG data will be uploaded to either the BCH SharePoint, a cloud-based platform that requires two-factor authentication for access, or a BCH administered, password protected external hard drive. SharePoint data in transit will be protected using best-in-class-encryption. The pseudonymisation key will not be shared with collaborators, so the data will be shared anonymously. All pseudonymised data downloaded to non-BCH computers will be deleted after use. After analysis, EEG data, including interpretation, will be uploaded onto the BCH SharePoint and the BCH administered, password protected secure external hard drive. Only the PI will know the password for the BCH administered external hard drive. A data sharing agreement will be signed by each centre we collaborate with.

We also plan to share anonymised EEG and associated clinical data with the Brain Data Science Platform (<https://bdsp.io/about/>), an international data repository for neurophysiological, brain imaging, genetics, omics, and associated clinical data and open-source software, which is run by the Clinical Data Animation Center and the McCance Center for Brain Health, Boston, MA.

## **11.Reporting adverse events**

The PI will record adverse reactions (AR) which may be directly related to the conduct of the study and document them in the participant's medical notes. ARs will be disclosed to the local research ethics committee providing ethical approval in an annual report. The participant's consultant will also be informed.

The PI and CI will assess AR causality as:

- Possibly: Temporal relationship of the onset of the event, relative to administration of the intervention, is reasonable but the event could have been due to another, equally likely cause.
- Probably: Temporal relationship of the onset of the event, relative to the administration of the intervention, is reasonable and the event is more likely explained by the intervention than any other cause.
- Definitely: Temporal relationship of the onset, relative to administration of the intervention, is reasonable and there is no other cause to explain the event, or a re-challenge (if feasible) is positive.

## **12.Indemnity**

BCH research and development office insurance will apply as appropriate.

## **13.Financial arrangements**

This main study is funded by an HEE/NIHR Doctoral Clinical and Practitioner Academic Fellowship (NIHR302896). The follow-up sub-study is funded by a research grant from Birmingham Women's and Children's Hospital Charity (37-6-206).

## **14.Authorship and publication**

The PI and CI, [name], [name] and [name] will form the basis of the publication committee and advise on drafting and submitting manuscripts following the advice of the entire research team.

**15.Amendment history**

| Amendment number | Date of amendment | Protocol version | Summary of amendment                                                                                                                                                   |
|-------------------------|--------------------------|-------------------------|-------------------------------------------------------------------------------------------------------------------------------------------------------------------------------|
| SA001                   | 25/07/2022               | v2.0                    | - Addition of SAFE:FIN sub-study, with funding
- Extension of recruitment period, with funding                                                                             |
| SA002                   | 08/11/2023               | v3.0                    | - Inclusion criteria revised to only neonates
- Extension to study duration to complete recruitment and 2-year follow-up sub-study
- Correction of typographical errors |
| SA003                   | 21/02/2024               | v4.0                    | - Added section on data sharing with collaborators                                                                                                                            |
| SA004                   | 29/04/2025               | v5.0                    | - Revision to study phase, moving from feasibility to observational cohort study. Objectives, outcome measures, and sample size revised accordingly.                          |

**Appendix: SAFE-Follow-up assessment of Infant Neurodevelopment (SAFE-FIN) sub-study**

**Population:** All neonates ( $\leq 4$  weeks corrected age) recruited to the SAFE Monitoring study at BCH in whom consent for future contact for determining development was obtained.

**Study duration:** With consent, the parents or guardians of participants will be re-approached at 22-26 months following surgery for a single assessment of neurodevelopment.

**Aims:** To 1) identify whether perioperative EEG activity is associated with long-term neurodevelopmental outcome, 2) assess feasibility of conducting follow-up neurodevelopmental assessments in this population.

**Primary objective:** Assess neurodevelopmental outcome following aortic arch surgery in neonates approximately 24 months post procedure using the Bayley-III scale of infant development.

**Secondary objectives:** Evaluate whether the duration of electrocerebral inactivity (ECI), or not achieving ECI prior to deep hypothermic circulatory arrest (DHCA); seizure burden and other EEG patterns are associated with Bayley-III scores. We will also determine whether late follow-up neurodevelopmental assessments are feasible in this population.

**Schematic of study design:** Participant flow through the sub-study is shown in figure 3. The PI will inform physiotherapy when neonatal SAFE Monitoring study patients are approaching the 24-month post procedure time point. The PI will agree several dates and times when the assessment could take place with physiotherapy and neurophysiology. The PI will then contact the families of recruited neonates and ask whether they would be interested in attending a follow-up appointment to assess their child's development. Where possible, these will be arranged in-line with BCH outpatient clinic appointments to reduce the burden on the family. The PI will confirm the appointment date and time with the parent or guardian and inform physiotherapy. All assessments will take place in the department of neurophysiology. The parent or guardian has already given written informed consent to be contacted about a follow-up assessment of their child's development. Physiotherapy will perform the Bayley-III assessment and document results on a dedicated score sheet. After the assessment, the physiotherapy team will email the PI the results of the assessment and provide the PI with the original hard copy for the site file. Bayley-III results will be shared with the child's consultant Paediatrician.

**Procedures:** All participants will be assessed using the third edition of the Bayley Scales of Infant and Toddler Development (Bayley-III) by a trained physiotherapist. This scale is an individually administered instrument that assesses developmental functioning of children between 1 month and 42 months of age. It is used to identify suspected delay in children consistent with current academia pertaining to child development. It can also assist paediatricians with intervention planning and other important clinical services. Additionally, the Bayley-III is designed to promote an understanding of the child's strengths and weaknesses in relation to five developmental domains: cognitive, language, motor, social-emotional, and adaptive behaviour. We anticipate the assessment appointment will last approximately 90 minutes, with an additional 90 minutes for analysis and interpretation of findings after the appointment.

**Primary outcome:** Adaptive behaviour score with percentile rank.

**Secondary outcomes:** The scaled and standard score, including percentile rank and age-equivalent for Language, Cognitive, Motor, and Social-Emotional Bayley-III domains. Number of participants recruited to follow-up assessment.

**Analysis:** Scores for each domain and subtest will be summarized using mean and standard deviation.

[figure not shown]

Figure 3: Participant flow through the sub-study

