### ii. Rationale & objectives

The addition of perioperative EEG for neonates undergoing aortic arch repair could ensure that:

- Those with abnormalities detected via EEG are identified preoperatively.
- Hypothermia is not excessive beyond the point of ECI, which has been reported to predict poor neurodevelopmental outcome.
- Current practice is sufficient to provide optimal neuroprotection.
- Perioperative subclinical seizures are identified and treated in a timely manner.

Currently there is a lack of evidence in this field which this study will contribute to.

The objectives of the study are to:

1. Evaluate whether the temperature at which ECI on EEG is achieved is a modifiable risk factor associated with the long-term neurodevelopmental outcomes of neonates undergoing aortic arch surgery with deep hypothermic circulatory arrest (DHCA).
2. Report perioperative EEG patterns, seizure burden, and neurodevelopmental outcome in this previously unmonitored group.

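### SAFE-FIN aims to relate perioperative EEG to Bayley-III scores, but the only Bayley-III analysis the protocol fixes is a mean and SD, which estimates no association

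*Protocol*

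**What the plan says.** The Appendix gives SAFE-FIN two aims. The first is to "identify whether perioperative EEG activity is associated with long-term neurodevelopmental outcome"; the second is feasibility of follow-up. Section 6 gives the same association as the reason for running the sub-study.

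The sub-study's primary objective is descriptive: "Assess neurodevelopmental outcome following aortic arch surgery in neonates approximately 24 months post procedure using the Bayley-III scale of infant development". Its secondary objectives are mainly associations. They ask whether the duration of ECI, or failure to reach ECI before circulatory arrest (DHCA), and "seizure burden and other EEG patterns are associated with Bayley-III scores".

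The primary outcome is "Adaptive behaviour score with percentile rank". The secondary outcomes include "The scaled and standard score, including percentile rank and age-equivalent for Language, Cognitive, Motor, and Social-Emotional Bayley-III domains".

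The Analysis entry is a single sentence: "Scores for each domain and subtest will be summarized using mean and standard deviation".

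In the main protocol, the first objective in Section 2.ii (also the primary objective in Section 1) is to "Evaluate whether the temperature at which ECI on EEG is achieved is a modifiable risk factor associated with the long-term neurodevelopmental outcomes".

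**The concern.** An association needs an analysis in which the score is set against an exposure. A mean and SD per domain describes the cohort as a whole. It gives no difference between children who did and did not reach ECI, no slope on ECI duration, and no contrast by seizure burden or EEG pattern. The protocol therefore fixes an analysis that cannot answer the sub-study's first aim.

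Two things are at stake. If the plan is followed literally, aim 1 and the association objectives go unanswered although every variable needed will have been collected. If it is not followed literally, the exposure, domain, model and covariates are chosen after the data are seen. With several exposures and five domains, that leaves much room for selective reporting.

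**Working it through.** **1. Aims against stated analyses**

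| Question | Where it is set | Analysis naming Bayley-III |
|---|---|---|
| Level of Bayley-III scores at about 24 months | Appendix, primary objective | Mean and SD (Appendix): adequate |
| ECI duration vs Bayley-III | Appendix, secondary objectives | None |
| ECI not reached before DHCA vs Bayley-III | Appendix, secondary objectives | None |
| Seizure burden vs Bayley-III | Appendix, secondary objectives | None |
| Other EEG patterns vs Bayley-III | Appendix, secondary objectives | None |
| Temperature at ECI vs long-term neurodevelopment | Sections 1 and 2.ii | None |

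**2. Does other text fill the gap?**

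- Section 5.ii lists relationships of reaching ECI, and of ECI duration, with clinical outcome measures. It does not define those measures, does not name Bayley-III, and does not relate seizure burden to outcome.
- Section 7 calls the secondary outcomes exploratory. That sets their status but supplies no analysis.
- Section 8 compares demographic, clinical and EEG variables by ECI status at DHCA, to find subgroups needing more neurocritical care. It names no Bayley-III score, and does not use ECI duration, seizure burden or temperature at ECI as an exposure.

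So the Appendix sentence is the only analysis of Bayley-III in the protocol.

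**3. The plan's own figure**

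SAFE-FIN has no sample size or precision figure. The main study's figure (Section 7) reproduces:

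- Expected number with ECI: 74 × 0.56 = 41.4 (stated: 41).
- Half-width for mean temperature: 1.96 × 2.9/√41 = 0.89 °C, or 0.92 °C with a t quantile (stated: ±0.9 °C).

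This concerns temperature only and does not bear on the Bayley-III question.

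**4. Precision of the missing analysis**

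Inputs: 41 children with ECI and 74 − 41 = 33 without (Section 7). The proportion assessed at two years is not in the documents; 70% is assumed and a range is shown. Results are in units of the within-group SD of the score, unadjusted, two groups.

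Half-width = t × √(1/n₁ + 1/n₀)

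| Assessed | ECI vs no ECI | 95% half-width |
|---|---|---|
| 100% | 41 vs 33 | 1.99 × 0.234 = 0.47 SD |
| 80% | 33 vs 26 | 2.00 × 0.262 = 0.53 SD |
| **70%** | **29 vs 23** | **2.01 × 0.279 = 0.56 SD** |
| 60% | 25 vs 20 | 2.02 × 0.300 = 0.61 SD |

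The difference detectable with 80% power at two-sided 5% (t-test) is 0.80 SD at 29 vs 23 and 0.66 SD at 41 vs 33.

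For temperature at ECI, only children who reach ECI contribute. The detectable correlation is tanh[(1.96 + 0.84)/√(n − 3)]: about 0.43 at n = 41 and 0.50 at n = 29.

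**The case against.** The strongest reply is that models, covariates and effect measures belong in a statistical analysis plan, which is not at hand. The Appendix sentence is not worded as exclusive, and it fits the sub-study's descriptive primary objective. The associations are already listed, with their exposures, as secondary objectives. Part of this stands: the mean and SD are right for what they serve, and the absence of modelling detail would not by itself be a finding. But the protocol does not defer the analysis. It states one, under a heading that covers the whole sub-study, and that analysis cannot address aim 1. This is a mismatch within the document.

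A second objection is that regressions on so few children will be imprecise and numerous. Five exposures (four named, plus temperature at ECI) by five domains is 25 models before adjustment. That is true. It is a reason to fix the order of priority and the exploratory label in advance.

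Two stronger readings are tempting and not supported:

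- *That percentile ranks are misused.* A reader might infer that percentile ranks and age-equivalents will be averaged. The sentence speaks of scores, and scaled and standard scores are properly summarised by mean and SD. The outcome lists mention percentile ranks and age-equivalents alongside the scores, and nothing says they will be averaged. At most, their summary is left unstated.
- *That the SAFE-FIN associations are the route to the main study's primary objective.* SAFE-FIN is the only source of two-year outcome data, since main-study follow-up ends at 30 days or discharge, whichever is sooner (Section 6). But its stated exposures do not include temperature at ECI, which is what the main objective concerns. An analysis limited to those exposures would still leave the main objective unanswered.

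**Conclusion.** The point holds in this form: aim 1 and the association objectives of SAFE-FIN have no matching analysis, because the only one stated for Bayley-III is a mean and SD over the cohort. This rests on the text alone and needs no assumption. The same gap leaves the main study's primary objective without an analysis.

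The precision figures are not the size of the defect. They show what the added analysis could deliver: about ±0.56 SD for the unadjusted ECI contrast under the assumed 70% follow-up, and between 0.47 and 0.61 SD for follow-up from 100% to 60%. They take the Section 7 split of 41 to 33 as given and ignore covariates. At that precision the results should be read as estimates, not as tests. The change should be made, and making it before outcome data are examined matters more than the exact model.

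**What to change.** Keep the mean and SD for scaled and standard scores, and add to the Analysis entry of the Appendix wording along these lines:

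*Each EEG exposure named in the secondary objectives (ECI duration, ECI not reached before DHCA, seizure burden, other EEG patterns) and, among participants who reach ECI, the temperature at ECI, will be related to the Bayley-III standard scores by linear regression. Adaptive behaviour will be analysed first, then the other domains. The difference or slope will be reported with its 95% confidence interval, unadjusted and adjusted for procedure type (isolated arch repair vs complex procedure including Norwood). All these analyses are exploratory. Adjustment for DHCA duration will be a sensitivity analysis only.*

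Procedure type is chosen because Section 3.i admits both isolated repairs and arch repair within more complex operations, and lesion complexity could plausibly affect both EEG and development. DHCA duration is kept out of the main model because the protocol does not define when ECI duration starts and stops. The two may overlap, and adjusting could remove much of the exposure.

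The cost is one paragraph and a modest set of regressions on data already planned for collection. The small downside is several exploratory models on few children, with wide intervals that the report must show plainly.
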